#### Procedure

Patients who might be eligible for participation will be contacted by their treating clinician and asked if they are interested in participating in the study. Clinicians will ask consent for sharing their contact information with the researchers after which interested patients will be informed about the study and screened by the researchers. After receiving written information about the study, patients will be given a consideration period of one week. If patients decide to participate after one week of consideration, written informed consent will be obtained first, and subsequently patients will complete the GPTS. If the GPTS score is > 40, patients are eligible for the study and the baseline assessment (T_0_) will continue. Following the baseline assessment, the baseline period of EMA will take place. After a week, patients are randomized to either VRcbt or CBTp. Patients allocated to either VRcbt or CBTp, will start with treatment. At the beginning of each session, participants complete the SDS and VAS. At the end of each session therapists complete the CGI. After the treatment period, a post-treatment (T_1_) takes place, followed by a seven days EMA. Finally, a follow-up (T_2_) assessment will be conducted six months after the start of treatment, followed by a final week of EMA. Patients who discontinue participation in the study at an early stage are requested to continue to participate in the measurements.

#### Early completions

In both treatment allocations, early completion will be deliberated when paranoid ideations and avoidance on the CGI scale are rated as zero in two consecutive sessions, and the target behaviour has been achieved. Foregoing applies to all the (virtual) situations formulated in the case formulations in agreement with the supervisor.

#### Data management

Patients data will be coded using a study ID. Personal information and informed consent will be stored separately and safely to ensure privacy. Data will be collected by using an electronic case report form and will be stored in the Research Electronic Data Capture (REDCap) [46]. To evaluate quality and integrity of the research, an independent study monitor will inspect annually.

#### Data analysis

Analysis will be performed according to the intention to treat principle. The groups will be compared at baseline. In case of baseline differences, variables will be added to further analyses as covariates. Potential covariates include age, sex, duration of illness and medication. The effect of VRcbt will be analysed by random intercept mixed effects regression models. The fixed effect of interaction between treatment group (VRcbt or CBTp) and time on momentary paranoia will be fitted as an estimate of the VRcbt treatment effect. Mean scores before and after treatment on each of the dependent variables will be compared between conditions. To determine the number of sessions needed for achieving clinically meaningful change, scores of patients on the VAS, the SDS and the GCI will be compared between conditions. The standard error of measurement (SEM) will be used to determine the proportion of participants with clinically meaningful change in each condition at each time point. Furthermore, cost-effectiveness analyses (CEA) will be conducted using the TiC-P and the EQ-5D-5L questionnaire. The economic evaluation consists of a CEA with improved momentary paranoia in daily life situations and a cost-utility analysis (CUA) with quality-adjusted life years (QALYs) gained as outcome. For both analyses, the incremental cost-effectiveness ratio (ICER) will be calculated as the between-group cost difference divided by the between-group effect difference. The ICER represents the additional costs needed (or saved) for establishing the VRcbt effect. The cost-utility ratio does the same per additional QALY gained. To handle uncertainty in the cost and effect data, nonparametric bootstrapping will be conducted to simulate 2500 ICERs.

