### Randomization and allocation concealment

Randomization will occur after completion of the baseline assessment. Block randomization will be used, with a block of eight random assignments for each participating mental health centre. The allocator will hide block size from the therapist and research assistants to prevent prediction of the next assignment. After a mental health centre has included eight patients, new blocks will be made available. Allocation to the two conditions will be in a 1:1 ratio. Randomization will be carried out by using the online randomization program www.randomizer.org by an independent researcher of the University Medical Center Groningen who is not involved in the trial. After the baseline assessment, the first author will enter the patients study ID into the online service and receive an email that details the patient’s allocation. The first author will then contact the therapist to inform them of the patients’ allocation. The therapist will then contact the patient about the allocation and to arrange the first therapy session.

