### Power and sample size calculation

In our previous RCT, comparing VRcbt with waiting list, the effect size on Ecological Momentary Assessment (EMA) paranoid delusions (see primary outcome measures) was 1.6 [15]. In the current study, the effect size is likely to be smaller with standard CBTp as active control condition. Assuming a much lower but still clinically relevant effect size of 0.6, a sample size of 122 (allowing 15% drop-out) will have a power of 80% to detect a multically significant treatment effect, using an alpha of 0.05 and a standard deviation of 1.1 for the outcome measure. Taking the multilevel structure of the data into account, with a (conservative) intra correlation coefficient of 0.8 and a commonly applied multiplication factor [20], 106 participants are needed for a unilevel equivalent *N* = 122.

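### Covariates are to be chosen by observed baseline differences, an open-ended rule that does almost nothing or leaves room for choice; centre, used to block randomisation, is not named

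*Protocol article*

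**What the plan says.** The Data analysis section first has the groups compared at baseline and then states the rule: "In case of baseline differences, variables will be added to further analyses as covariates". The candidates follow: "Potential covariates include age, sex, duration of illness and medication". No test, threshold or size of difference is given, and the article does not say whether a chosen covariate enters as a main effect or also interacts with time.

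The same section defines the primary model: "The effect of VRcbt will be analysed by random intercept mixed effects regression models". It takes the treatment effect from the interaction: "The fixed effect of interaction between treatment group (VRcbt or CBTp) and time on momentary paranoia will be fitted as an estimate". The comparison of the number of sessions needed for clinically meaningful change is described separately and is not framed as an interaction.

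Under Randomization and allocation concealment the article says: "Block randomization will be used, with a block of eight random assignments for each participating mental health centre". It adds: "Allocation to the two conditions will be in a 1:1 ratio". Randomisation is therefore stratified by centre. Centre is not among the named candidate covariates or in the description of the model.

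**The concern.** Under correct randomisation any baseline difference between arms is a chance event. A rule triggered by it selects covariates for the wrong reason. What makes a covariate useful is that it predicts the outcome, and a strong predictor that happens to be balanced would be left out. With no criterion and an open list, the content of the adjusted models is settled only once the data are visible.

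It is also doubtful that the rule does what it is meant to do. The primary estimate is a group-by-time interaction, in other words a difference between arms in change. A characteristic that is constant over time and enters as a main effect shifts all of a patient's occasions equally, so it should drop out of that contrast.

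Finally, an analysis would normally reflect the factor by which randomisation was blocked. At stake are a fixed analysis and some precision.

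**Working it through.** **Inputs from the article.** "Assuming a much lower but still clinically relevant effect size of 0.6"; "using an alpha of 0.05 and a standard deviation of 1.1 for the outcome measure"; 80% power, 15% dropout, an intra-correlation of 0.8, sample sizes of 122 and 106 (Power and sample size calculation); 1:1 allocation in blocks of eight per centre.

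**Reproducing the plan's figure, to fix the scale.** Reading 0.6 as a raw difference with SD 1.1, two-sided alpha 0.05:

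- Per arm: 2 × (1.960 + 0.842)² × 1.1² / 0.6² = 52.8, so 53, or 106 in total.
- Dropout: 106 × 1.15 = 121.9, so 122.
- Multilevel factor, three occasions: (1 + 2 × 0.8)/3 = 0.867, and 122 × 0.867 = 105.7, so 106.

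The figures reproduce and do not depend on the covariate rule.

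**How often the rule would fire.** Assume that a difference means p < 0.05 and that the four named candidates are independent (the article states neither). The chance that at least one is flagged in a correctly randomised trial is 1 − 0.95⁴ = 0.185, about 19%.

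**Effect on the planned interaction.** With complete data and one value per occasion, the interaction estimate is the difference between arms in mean change. A time-constant covariate cancels from each patient's change. The expected standard error is √[(2/53) × 2 × (1 − 0.8) × 1.1²] = √0.01826 = 0.135. As a check, random-intercept models were fitted to simulated trials: 106 patients, 7 centres (assumed), a time-constant covariate unrelated to change, 2 or 3 occasions, dropout at random, and 40 trials per scenario. The table gives the largest absolute shift in the interaction estimate relative to the model without covariates.

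| Scenario | Covariate main effect | Centre main effect | Covariate-by-time | SE without covariates |
|---|---|---|---|---|
| Complete, 2 occasions | 0 | 0 | 0.052 | 0.135 |
| Complete, 3 occasions | 0 | 0 | 0.076 | 0.135 |
| 15% dropout, 2 occasions | 0.018 | 0.014 | 0.032 | 0.145 |
| 15% dropout, 3 occasions | 0.020 | 0.016 | 0.050 | 0.147 |

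The zeros are exact to rounding (below 2 × 10⁻¹⁴). Main-effect adjustment left the standard error essentially unchanged. The largest main-effect shift is 0.020/0.6 = 3% of the design effect. Covariate-by-time terms moved the estimate by up to 0.076/0.135 = 0.56 of a standard error, although the simulated covariate did not predict change at all.

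**Centre.** As a main effect, centre behaves like any other time-constant covariate (third column). It can matter for the primary contrast only if centres differ in change. This was simulated on change scores, assuming 7 centres, residual change-score SD 1.1, blocks of eight within centre, effect 0.6 and 4,000 trials per cell.

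| Centre SD on change | Share of variance | Type I error, centre omitted / included | Power, centre omitted / included |
|---|---|---|---|
| 0 | 0 | 0.048 / 0.049 | 0.79 / 0.80 |
| 0.3 | 0.09/(0.09 + 1.21) = 7% | 0.048 / 0.053 | 0.78 / 0.79 |
| 0.6 | 0.36/(0.36 + 1.21) = 23% | 0.025 / 0.048 | 0.73 / 0.79 |

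The simulation error of a power near 0.79 is √(0.79 × 0.21/4000) = 0.006, so the one-point difference at SD 0.3 is barely distinguishable from noise.

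**The case against.** The strongest reply is that the rule is nearly inert where it counts. If covariates enter as main effects, the primary interaction and its standard error hardly move, so there is little room to steer the primary p-value. This stands for that reading. A reader might infer that the rule leaves the primary p-value open. The article does not support that in general, because it does not say how covariates enter. The inference needs covariate-by-time terms. The reply does not rescue the rule, however: on one reading it does nothing, and on the other it brings in a choice made after seeing the data. The article applies it to further analyses in general, which include comparisons that are not interactions.

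A reader might also infer that omitting centre makes the primary standard error too wide whenever centres differ. That is too strong. Stable differences in level between centres cancel from the interaction just as other covariates do; only differences in change matter. Nor is any false-positive inflation at issue, since omission makes the test conservative.

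Third, this is a condensed article. Its covariate list is expressly not exhaustive, the levels of the random intercepts are not spelled out, and a statistical analysis plan may name centre. This is fair, and it makes centre the secondary part of the point. It does not reach the baseline-difference rule, which is stated outright; a later document that defined a difference more precisely would still be carrying out the same rule.

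Finally, it would be wrong to say that no prognostic variable is used when the rule does not fire. Baseline paranoia is already in the model as the T0 occasion.

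**Conclusion.** The point holds in a limited form. The firm part is the explicit rule: selection by chance imbalance, without a criterion and from an open list, is a poor way to fix covariates in a randomised trial.

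Its effect on the planned primary estimate is nil with complete data and at most about 0.02 against 0.6 with 15% dropout, if covariates enter as main effects. The 0.02 assumes dropout unrelated to the covariate and one summary value per occasion. If covariates interact with time, or in analyses such as sessions to meaningful change, the estimate can depend on the choice. The 19% is illustrative and rests on a 5% test and independent candidates.

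The omission of centre is conditional. It costs about one point of power at an assumed centre SD of 0.3 and about six points at 0.6. The documents give neither the number of centres nor how far they differ in change, and the result depends on centre SD relative to the change-score SD, itself assumed. The documents do not support a claim that the primary test is invalid or anti-conservative.

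**What to change.** Delete the baseline-difference rule and report the baseline table descriptively. Before outcome data by arm are seen, pre-specify one covariate set to be used whatever the observed imbalance:

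- the baseline value of the outcome;
- centre, with small centres pooled or as a random effect;
- a short fixed list, such as age and sex.

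Enter these so that they act on the post-baseline comparison. Either model T1 and T2 with adjustment for the T0 value, or keep T0 as an occasion in the longitudinal model, where it already carries the baseline outcome, and add covariate-by-visit terms for centre and the fixed list. State the same set for the analyses that are not interactions.

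The cost is revised analysis wording and a few degrees of freedom: 6 for centre as a fixed effect with the assumed 7 centres, for each post-baseline comparison. In the simulation with no centre differences, including centre cost no power. The first option also replaces the published interaction estimator, so it should be recorded as a change to the primary analysis. Sample size, visits and procedures are unaffected.

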**Methods:**

A total of 106 patients with DSM-5 diagnosis of psychotic disorder and at least moderate level of paranoid ideations will be recruited for this multicentre randomized controlled trial (RCT). Patients will be randomized to either VRcbt or standard CBTp for paranoid delusions. VRcbt consists of maximum 16 sessions in virtual social situations that trigger paranoid ideations and distress, delivered in an 8–12 week time frame. Standard CBTp also consists of maximum 16 sessions including exposure and behavioural experiments, delivered in an 8–12 week time frame.

The two groups will be compared at baseline, post-treatment and six months follow-up. Primary outcome is the level of paranoid ideations in daily life social situations, measured with ecological momentary assessments (EMA) at semi-random moments ten times a day during seven days, before and after treatment. Every session, participants and therapists will rate the level of paranoid ideation and global clinical impression.

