### Materials and measurement instruments

#### Primary outcome measure

##### Momentary paranoia in daily life social situations

Level of momentary paranoia in daily life is measured with *Ecological Momentary Assessment* (EMA). EMA is a structured diary method in which patients are asked to report their momentary thoughts, feelings and symptoms, as well as the (appraisal of the) social context in daily life [23]. Momentary paranoia is measured ten times a day for seven consecutive days before treatment, after treatment and three months after treatment. Items assessing momentary paranoia include “I feel that others might hurt me”, “I feel that others dislike me” and “I feel suspicious” [24]. Items are scored on a 7-point Likert scale ranging from 1 (not at all) to 7 (very). Mean total scores are calculated based on all 70 measurements. The EMA allows investigation of experiences occurring in daily life environments instead of retrospective self-reflection on feelings and behaviour [25]. Therefore, the EMA is less sensitive to recall bias and has a high ecological validity [23].

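### The group-by-time interaction names no deciding visit, and on its ordinary reading it uses the baseline score less efficiently than adjustment would

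*Protocol article*

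**What the plan says.** Under Data analysis, the article states the model: "The effect of VRcbt will be analysed by random intercept mixed effects regression models". It then says how the benefit of VRcbt is to be estimated: "The fixed effect of interaction between treatment group (VRcbt or CBTp) and time on momentary paranoia will be fitted as an estimate". The next sentence describes a comparison of two occasions: "Mean scores before and after treatment on each of the dependent variables will be compared between conditions".

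The visits are described in two ways:

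- **Two occasions.** The Methods part of the Abstract has the primary outcome measured "at semi-random moments ten times a day during seven days, before and after treatment". The mean-score sentence under Data analysis agrees with this.
- **Three occasions.** The primary outcome section says: "Momentary paranoia is measured ten times a day for seven consecutive days before treatment, after treatment and three months after treatment". The Design section compares the conditions at T0, T1 and T2. The Discussion adds the hypothesis that the difference is maintained at follow-up.

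On covariates, the rule is: "In case of baseline differences, variables will be added to further analyses as covariates". The candidates are then listed: "Potential covariates include age, sex, duration of illness and medication". Baseline momentary paranoia is not among them. The article does not state how time is coded, or whether the two arms share a baseline mean.

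**The concern.** A single interaction is a complete definition of the effect when there are two visits. With three, it can mean at least two things.

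- **Numeric time.** The interaction is a difference in slopes, which depends almost entirely on the first and last visits.
- **Categorical time.** There is one term for T1 and one for T2, and the text does not say which decides superiority.

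The trial is titled a superiority trial, so its headline claim rests on this one test.

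There is also a smaller question of efficiency. Randomisation makes the expected baseline means equal. A model that estimates them separately does not use that fact, and so carries chance baseline imbalance into the estimate at full weight.

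**Working it through.** **Inputs from the article (Power and sample size calculation).** Difference 0.6, SD 1.1, alpha 0.05, power 80%, drop-out 15%, correlation 0.8, final N 106. The check below supports reading 0.6 as raw scale points, alpha as two-sided and 0.8 as the correlation between visits.

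**Reproducing the plan's figure.** A two-sided comparison of two means with difference 0.6 and SD 1.1 needs 53 per arm, 106 in total. Adding 15% gives 106 × 1.15 = 121.9, or 122. The repeated-measures factor (1 + (T − 1)rho)/T at rho = 0.8 gives:

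- T = 3: 122 × 2.6/3 = 105.7, or 106, as stated.
- T = 2: 122 × 1.8/2 = 109.8, or 110.

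So the sample size was worked out for three measurements, although other passages describe a before/after comparison.

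**Weight of T1 under numeric time.** The slope weights are (t − mean)/SS.

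- t = 0, 1, 2: weights −0.5, 0, 0.5. T1 has no weight.
- t = 0, 12, 26 weeks (upper end of the treatment window, follow-up six months after the start): weights −0.0374, −0.0020, 0.0394. The T1 weight is −5% of the T2 weight.

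For illustration, take 90 evaluable participants (106 × 0.85 = 90.1, so 45 per arm), rho = 0.8 and coding 0, 1, 2. The standard error of the slope difference is √(2 × 1.21 × 0.2 / (2 × 45)) = 0.0733. The effect patterns are assumed:

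| True difference at T1, T2 | Expected slope difference | Power, slope | Power, T1 contrast |
|---|---|---|---|
| 0.6, 0.6 | 0.30 | 98% | 98% |
| 0.6, 0.3 | 0.15 | 53% | 98% |
| 0.6, 0 | 0 | 2.5% (one tail) | 98% |

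**Two terms under categorical time.** Under the equal correlation that a random intercept implies, the T1 and T2 change scores correlate 0.5 for any rho. If each were tested at 5% and either could count as success, the familywise error would be about 9%.

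**Use of baseline.** Relative to a post-treatment comparison alone (factor 1), the variance of the T1 effect has these factors:

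- interaction with separate baselines: 2(1 − rho)
- baseline as covariate, or a common baseline mean: 1 − rho²
- ratio of the first to the second: 2(1 − rho)/(1 − rho²) = 2/(1 + rho)

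Power is for difference 0.6, SD 1.1 and 45 per arm, by normal approximation:

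| rho | Interaction factor | Adjusted factor | Ratio | Power, interaction | Power, adjusted |
|---|---|---|---|---|---|
| 0.8 (article) | 0.40 | 0.36 | 1.11 | 98.4% | 99.1% |
| 0.5 (assumed) | 1.00 | 0.75 | 1.33 | 73.5% | 84.8% |
| 0.3 (assumed) | 1.40 | 0.91 | 1.54 | 59.0% | 77.4% |

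At rho = 0.8 the interaction already cuts the variance by 60% against post-treatment alone (1 to 0.40). Adjustment cuts a further 10% (0.40 to 0.36). Below rho = 0.5 the interaction is less precise than ignoring baseline.

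**The case against.** The best defence is that the article can be read as a two-visit plan. The sentence after the interaction speaks of scores before and after treatment, the Abstract does the same, and the Discussion treats follow-up as a question of maintenance. If only T0 and T1 enter, there is one interaction term, it is the T1 contrast, and neither coding nor multiplicity arises. Time coding and the treatment of baseline are also ordinary content of an analysis plan that is not shown. Even with three visits, a joint two-degree-of-freedom test would hold the error at 5% and has 96% power in the 0.6-then-0.3 pattern.

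Much of this stands. No passage states numeric time or two unadjusted tests, so a reader who infers that the headline test ignores T1, or that its error rate is 9%, goes beyond the text. These are consequences of readings that the wording leaves open. The defence does not remove the inconsistency, however. The primary outcome section and Design use three visits, the sample size reproduces only with three, and no passage labels T1 as primary.

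A reader might also infer that baseline information is thrown away. The document does not support that: T0 is in the model as an outcome, and the interaction is a change-from-baseline contrast. Nor does it support a large loss of power, because its only correlation is 0.8 and the gain there is 0.7 points. Separate baselines are themselves the default reading, not a statement in the article. The interaction is a valid, unbiased analysis, so this part is an improvement in efficiency and not the correction of an error.

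**Conclusion.** The point holds in two parts of unequal weight.

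The main part is that the article defines the effect by an interaction without naming the deciding visit, and its sections alternate between two and three visits. The possible cost depends on a coding that is not stated. It is nil if only T0 and T1 enter. It is small under numeric time if the effect is fully maintained, and severe under numeric time if the effect wanes (53% against 98% power in the assumed 0.6-then-0.3 pattern).

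The lesser part is that, if baselines are estimated separately, the T1 term uses baseline less efficiently than adjustment does. The variance ratio is 1.11 at the article's 0.8, worth 0.7 points of power. It reaches 1.33 or 1.54 only at assumed correlations of 0.5 or 0.3. Adjustment is therefore cheap protection in case 0.8 proves too high, and under these formulas it is never less precise. All variance figures assume complete data and equal correlation between visits.

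**What to change.** In the Data analysis section, state that visit is fitted as categorical, that the VRcbt minus CBTp difference in momentary paranoia at T1 is the single primary contrast, and that the difference at T2 is secondary. Include baseline EMA paranoia through a baseline mean common to both arms, or as a covariate with T1 and T2 as outcomes, whatever imbalance is observed. Use the same form for secondary outcomes measured at baseline. Bring the Abstract, Design and primary outcome sections into line with this.

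The cost is a sentence or two in the analysis section and matching wording elsewhere. No extra data or participants are needed. The change should be made before outcomes are examined by allocation.

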### Objectives

In this RCT, we aim to investigate differences between VRcbt and CBTp in their effect on the level of paranoid delusion in daily life, level of social activities, proportion of time spent in social company, levels of distress, anxiety and depression. In addition, we aim to investigate the differences between groups in the mean number of sessions needed for clinically meaningful improvement of paranoid delusions in daily life. Finally, we aim to assess the differences between health care costs and production losses over the intervention and follow-up period. We hypothesize that VRcbt is more effective and cost-effective than CBTp for treating paranoid delusions and improving daily life social functioning of patients with schizophrenia and related psychotic disorders.

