### Interventions

#### VRcbt

VRcbt will be delivered by trained therapists, with at least a postgraduate qualification in CBT, and with a minimum of half a year of experience in psychosis treatment.

VRcbt consists of maximum 16 sessions within an 8–12-week time-frame. Sessions will last maximum 75 min, of which 40 min are spent in virtual social situations that trigger paranoid delusions and distress. The remaining time will be used to plan and reflect on exercises and to complete the session measurements. Throughout the first sessions, therapists construct individually tailored case-formulations based on CBTp, in close collaboration with the patient in order to create a shared understanding of the current paranoid ideas, related feelings and behaviour. Subsequently, patients are guided by therapists who help them drop safety behaviours and test their paranoid beliefs. The following animated virtual social environments can be used, i.e., café, shopping street, supermarket, bus ride, office and living room. The level of difficulty of the particular social environment can be modified by adjusting the number, gender and ethnic appearance of virtual characters (avatars) present in the situation. The level of hostility and suspicious behaviour can be modified as well. Personalized interactive scenarios can be role-played. The therapist talks via a microphone (with voice distortion) as an avatar and operates the avatars’ body movements. Patients wear an Oculus Rift head-mounted display and navigate through the virtual environments using a controller.

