#### CBTp

CBTp will be delivered by trained therapists, with at least a postgraduate qualification in CBT, and with a minimum of half a year of experience in psychosis treatment. CBTp also consists of maximum 16 sessions which last up to 75 min within an 8–12 week time-frame. CBTp emphasises cognitive techniques, such as cognitive restructuring and behavioural interventions, including exposure and behavioural experiments. CBTp focuses on exercises aimed at reappraisal of paranoid beliefs’ meaning to reduce distress and improve coping in daily life. Throughout the first sessions, therapists construct individually tailored case-formulations based on CBTp, in close collaboration with the patient in order to create a shared understanding of the current paranoid ideas, related feelings and behaviour. Each session, time will be reserved for planning and reflecting on exercises and completing the session measurements. The Dutch CBT protocol for delusions will be applied (gedachtenuitpluizen.nl).

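### The planned analysis of session scores and SEM-based proportions does not estimate the stated objective, the mean number of sessions to clinically meaningful improvement

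*Protocol article*

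**What the plan says.** The Objectives section of the protocol article sets out to compare "differences between groups in the mean number of sessions needed for clinically meaningful improvement of paranoid delusions in daily life". The section on clinically meaningful change collects patient ratings (VAS and SDS) at the start of every session and the therapist's CGI at the end of every session, expressly to test the number of sessions needed.

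The Data analysis section then gives the method in two steps. First, "scores of patients on the VAS, the SDS and the GCI will be compared between conditions" (GCI is evidently the CGI). Second, the SEM "will be used to determine the proportion of participants with clinically meaningful change in each condition at each time point". It names no multiple of the SEM, and it does not say whether a time point is a therapy session or one of the assessments T0, T1 and T2.

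Two design features bear on this. Both arms have the same cap: "VRcbt consists of maximum 16 sessions within an 8–12-week time-frame", and "CBTp also consists of maximum 16 sessions which last up to 75 min". Therapy can also end sooner because of good outcome: "early completion will be deliberated when paranoid ideations and avoidance on the CGI scale are rated as zero in two consecutive sessions", provided that the target behaviour has been achieved, in all situations of the case formulation and with the supervisor's agreement.

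**The concern.** The number of sessions needed to reach a criterion is a time-to-event quantity on a session scale, and the two stated steps are not analyses of such a quantity. A comparison of scores gives a difference in severity. A proportion at a time point gives a share of patients. Neither assigns a number of sessions to a patient, and the text gives no route from them to the mean that the Objectives name.

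An analyst who tries to bridge the gap meets two problems. A patient who has not reached the criterion by the last session has no value, so a plain mean exists only among achievers, a group formed after randomisation. And because the VAS, SDS and CGI for this objective are tied to sessions, a patient who finishes early supplies no later ratings. The request in the Procedure section that patients who stop early continue with measurements cannot supply ratings from sessions that do not take place.

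At stake is the efficiency claim. The Discussion suggests that the effect of VRcbt may occur within fewer sessions than that of CBTp.

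**Working it through.** The documents give no design figure for this objective, so there is nothing of the plan's own to reproduce. The sample sizes of 122 and 106 concern the EMA primary outcome. The 16-session cap comes from the protocol. The per-session chances of change, the leaving rates and the error model below are assumptions, because the documents state none of them.

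**1. Achievers only against all patients.** Let h be a constant chance per session of first reaching the criterion, counted from session 1.

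- Share reaching it by session 16: F = 1 − (1 − h)^16.
- Restricted mean to 16 sessions, all patients: RM = F / h.
- Mean among achievers only: A = (RM − 16 × (1 − F)) / F.

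For h = 0.10: F = 0.815, RM = 0.8147 / 0.10 = 8.1, A = (8.147 − 16 × 0.1853) / 0.8147 = 6.4.

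For h = 0.067: F = 0.670, RM = 0.6703 / 0.067 = 10.0, A = (10.005 − 16 × 0.3297) / 0.6703 = 7.1.

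| Assumed h, faster v slower arm | Reach criterion by session 16 | Achievers-only mean (difference) | Restricted mean (difference) |
|---|---|---|---|
| 0.10 v 0.067 | 81% v 67% | 6.4 v 7.1 (0.7) | 8.1 v 10.0 (1.9) |
| 0.08 v 0.05 | 74% v 56% | 6.8 v 7.4 (0.6) | 9.2 v 11.2 (2.0) |
| 0.05 v 0.033 | 56% v 42% | 7.4 v 7.8 (0.4) | 11.2 v 12.6 (1.4) |

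In each case the achievers-only difference is well under half of the restricted-mean difference.

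**2. Early completion.** Suppose a fraction q of those who reach the criterion leaves two sessions later. Those who reach it by session 13 and leave are absent at session 16. The proportion changed among attenders at session 16 is (F16 − q × F13) / (1 − q × F13), with F13 = 0.746 for h = 0.10 and 0.594 for h = 0.067.

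- q = 0: 81% v 67%, gap 14 points.
- q = 0.3 in both arms: 76% v 60%, gap 16 points.
- q = 0.5 in both arms: 70% v 53%, gap 17 points.
- q = 0.5 in the faster arm and 0.3 in the slower: 70.4% v 59.9%, gap 11 points.

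Both proportions fall, and the gap may widen or narrow depending on the leaving rates.

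**3. The SEM as threshold.** A change score carries the error of two measurements, so its error SD is √2 × SEM. For a patient with no true change, the chance of crossing k × SEM at one time point is 1 − Φ(k/√2). The chance of crossing at least once in S later sessions, with a shared baseline error and independent session errors, is ∫ φ(z) [1 − (1 − Φ(z − k))^S] dz.

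| Threshold | One time point | At least once in 15 later sessions |
|---|---|---|
| 1 SEM | 24% | 74% |
| 1.96 SEM | 8% | 42% |
| 1.96 × √2 SEM | 2.5% | 18% |

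At 1 SEM, the cumulative chance over all unchanged patients passes one half at the fourth post-baseline session (44.8% by the third, 50.6% by the fourth).

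**The case against.** The strongest reply is that this is a condensed article. How non-achievers and early completers are counted, and which multiple of the SEM applies, are details that an analysis plan commonly holds, and the article does state intention to treat. That stands as far as it goes: the article is silent on these rules, and it does not say that only achievers will be averaged. But the objective and the method are both stated here, and they do not match. An analysis plan that kept to the stated method would still produce no number of sessions.

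Three stronger readings are tempting, and the documents do not support them.

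- A reader might infer that the SEM criterion counts mostly noise as change. No multiple of the SEM is given. Even at 1 SEM, 24% of unchanged patients cross at one time point, a minority. With assumed reliability of 0.7 to 0.9, mean true change of 0.3 to 1.6 SD and an SD of true change of 0.5 to 0.8, a simulation put the share of 1-SEM changers whose true change was zero or negative at 0% to 10%. The 74% needs a first-crossing rule over repeated sessions, which the text does not state. If time points are T0, T1 and T2, it does not arise for the planned proportions.
- A reader might infer that early completion makes VRcbt look worse. With equal leaving rates both arms fall and the gap does not shrink. Early completion is also deliberated under several conditions and is not automatic, and no rate is given.
- A reader might infer that the economic evaluation is undermined. It uses the TiC-P, the EQ-5D-5L and momentary paranoia. Sessions to change is not an input.

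**Conclusion.** The point holds in this form: the stated analysis does not estimate the stated objective, and the 16-session cap together with outcome-dependent early completion makes the number of sessions a censored quantity for which the text gives no rule. Under the assumed rates, averaging over achievers would show a difference of 0.4 to 0.7 sessions where the restricted mean to 16 sessions shows 1.4 to 2.0. These figures rest on a constant per-session chance of change and illustrate scale only. They do not predict this trial's result. The direction of any bias from early completion cannot be fixed from the documents.

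The threshold is a subordinate matter. It becomes serious only if the number of sessions is taken from a first crossing at a small multiple of the SEM. The plan should be changed, but this is a secondary objective and the primary EMA comparison is untouched.

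**What to change.** In Data analysis, replace the two sentences on this objective with a time-to-event analysis of sessions to first clinically meaningful change in all randomised patients. Report Kaplan-Meier curves and the between-group difference in restricted mean to 16 sessions, or use a discrete-time model. Censor non-achievers at their last session, and count early completers who met the criterion as events at the session where they met it. Censoring at the last session assumes that those who leave resemble those who stay, so add a sensitivity analysis for patients who leave without having met the criterion.

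State the threshold in terms of the error of a difference, for example 1.96 × √2 × SEM, with the source of the reliability estimate. Say which instrument defines the event, and whether a time point is a session or an assessment. The choice of lead instrument, and whether change must hold at two consecutive sessions, are matters of preference that need only be fixed in advance.

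The cost is analysis wording, since the session ratings are already collected. The downside is that a stricter threshold gives fewer events and hence less precision.
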